#### Experiment III—Lamotrigine (LTG) in patients with NF1

Participants receive 300 mg single dose LTG or placebo 2 h before TMS [11]. After at least 7 (up to 60) days, a cross-over takes place: participants receive placebo or 300 mg single dose LTG 2 h before TMS (Table 2, Additional file 1).

**Table 2 Tab2:** Schedule of procedures and visits patient group 2, NF1

*Study overview medication*	**Baseline visit (or day 1)**	**Visit 1 (day1)** **D1**	**Visit 2 (7–60 days after V 1)** **D8–61**
		Exp. III: Lamotrigin (LTG) or Placebo	
Informed consent	**X**		
Eligibility criteria	**X**		
Demographics	**X**		
Medical/surgical history	**X**		
Vital signs	**X**	**X**	
Pregnancy test^a^	**X**	**X**	
Randomization		**X**	
Exp. III: LTG or PLC) Single dose		**X**	**X** **(cross-over)**
TMS (EMG integrated)^a^		**X**	**X**
TAP		**X**	**X**
Concomitant medication	**X**	**X**	**X**
AE/SAE		**X**	**X**

^a^To be performed after having obtained informed consent; if baseline is less than 5 days prior to V1, a second pregnancy test is not necessary

^b^TMS to be performed 2 h after intake of LTG

Experiments I and II take place with a sufficient time gap on the same set of patients (Fig. 1). It is not possible to conceal treatment in a triple cross-over design in group 1, which is why two separate tests have been planned on group 1.

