### Study population

Inclusion criteria are defined as follows: (1) Group 1: NS, Group 2: NF1 (both genetically assured); (2) age ≥ 16 years; (3) signed informed consent of the adolescent (16–17 years of age) who is capable to give his consent and understand the aim and rationale of the study and of the legal guardian; (4) signed informed consent of persons who are ≥ 18 years old and capable to give their consent. In case of doubts, an independent medical practitioner will evaluate the capacity to consent; (5) male and female participants who are not capable of bearing children or who use a method of contraception that is medically approved by the health authority of the respective country.

Exclusion criteria are (1) epilepsy, (2) participants taking medication with known central nervous system (CNS) effects, (3) severe mental retardation, (4) side effects during previous medication with and contraindications for LTG and/or LOV and/or transcranial magnetic stimulation (TMS), (5) psychiatric diseases, (6) previous history of allergic reactions with LTG and LOV medications, (7) potentially unreliable patients, (8) patients who are not suitable for the study in the opinion of the investigator, (9) pregnancy (incl. positive urine pregnancy test) and (10) persons who are incapable of giving consent or do not understand the aim or rationale of the study.

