### Interventions

Participants are randomized into either one out of the three approaches (exp. I–III). Three randomizations take place—one for each experiment. Patients are randomly assigned to receive either first verum then placebo, or vice versa. The randomization lists were created using RANCODE professional 2015. Randomization is performed block-wise. The randomization list was provided to the pharmacy for blinding, labelling and distribution of trial medication. For the case of emergency unblinding, a second set of sealed envelopes includes the information on the type of medication for each randomization number and is stored at the trial site. The integrity of the envelopes is monitored until end of study.

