#### Experiment II—Lovastatin (LOV) in patients with NS

Participants receive 200 mg LOV or placebo daily for 4 days prior to TMS. On the day of TMS, the medication is given 3 h before starting TMS corresponding to the peak plasma concentration of LOV [12]. After at least 14 (up to 60) days, a cross-over takes place: participants receive placebo or 200 mg LOV daily for 4 days prior to TMS (Table 1, Additional file 1). On the day of TMS, the medication is given 3 h before starting TMS.

**Table 1 Tab1:** Schedule of procedures and visits patient group 1, NS

*Study overview medication*	**Base-line (or day 1)**	**Visit 1 (day 1)** **D1**	**Visit 2 (min. 7—60 D after V 1)** **D8–61**	**Visit 3 (min. 14–60 D after V2)** **D22–121**	**Visit 4 (3 D after V3)** **D25–124**	**Visit 5 (min. 14–60 D after V4)** **D39–184**	**Visit 6 (3 D after V5)** **D42–187**
		**Exp. I: Lamotrigine (LTG) vs. placebo, single dose (with cross-over)**		**Exp II: Lovastatin (LOV) vs. placebo 4 days (with cross-over)**			
Informed consent	**X**						
Eligibility criteria	**X**						
Demographics	**X**						
Medical/surgical history	**X**						
Vital signs	**X**	**X**	**X**	**X**		**X**	
Pregnancy test^a^	**X**			**X**			
Randomization		**X**		**X**			
Exp. I: LOV or PLC) Four days				**X**	**X**	**X** **(cross-over)**	**X**
Exp. II: LTG or PLC) Single dose		**X**	**X** **(cross-over)**				
TMS (electromyography (EMG) integrated)^b^		**X**	**X**		**X**		**X**
TAP		**X**	**X**		**X**		**X**
Concomitant medication	**X**	**X**	**X**	**X**	**X**	**X**	**X**
AE/SAE		**X**	**X**	**X**	**X**	**X**	**X**

^a^To be performed after having obtained informed consent; if baseline is less than 5 days prior to V1, a second pregnancy test is not necessary

^b^TMS to be performed 3 h after intake of LOV and 2 h after intake of LTG

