### Trial status

The current protocol version number is “Final 5.0 AM 3.0”, date 9/21/2020. Recruitment finished on 3/30/2023 prematurely due to unforeseen difficulties in recruitment of patients. Recruitment was still open on initial submission of the manuscript. Recruitment began in March 2018, and an actual number of 16 participants have been enrolled. A large panel including the sponsor-delegated person, the head of German Network of RASopathy Research (GeNeRARe) and the Sponsors representative for risk-based quality management decided to prematurely close the recruiting and to terminate the study in retrospect on 2/20/2023 due to the last patient last visit (LPLV) taking place on 2/9/2023.

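### The printed visit schedules mark no pregnancy test before second-period dosing (V2 in both groups, V5 in Noonan syndrome), so placebo-first women reach active drug on an old test

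*Protocol article*

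**What the plan says.** The Interventions section of the protocol article states: "Patients are randomly assigned to receive either first verum then placebo, or vice versa". In each experiment, then, one sequence gives placebo in period 1 and active drug in period 2. For Experiment III the second period is timed as "After at least 7 (up to 60) days, a cross-over takes place", and Experiment I uses the same window. For Experiment II, Table 1 heads the cross-over visit "Visit 5 (min. 14–60 D after V4").

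Exclusion criterion 9 under Study population is "pregnancy (incl. positive urine pregnancy test"). Inclusion criterion 5 admits "male and female participants who are not capable of bearing children or who use a method of contraception that is medically approved".

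The pregnancy-test row is marked as follows:

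- **Table 1 (NS):** baseline and V3. Blank at V1, V2, V4, V5 and V6.
- **Table 2 (NF1):** baseline and V1. Blank at V2.

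Footnote a, under both tables, says that "if baseline is less than 5 days prior to V1, a second pregnancy test is not necessary". Eligibility criteria are marked at baseline only.

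**The concern.** V2 and V5 are the visits at which half of the sequences switch from placebo to active drug. For a woman on such a sequence, the scheduled test protects the placebo period, and the active period follows up to about two months later with no scheduled recheck. Followed as printed, the schedule could give lamotrigine or lovastatin to a woman who has become pregnant since her last test, although pregnancy is an exclusion criterion.

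The schedule also applies two standards. Before V1 it lets a baseline test stand only if it is less than 5 days old. Before V3 it tests again after a gap of 14 to 60 days. Before V2 and V5, after gaps of similar or greater length than those that trigger a test elsewhere, it does not. Under blinding, V5 is as likely as V3 to start active lovastatin if allocation is balanced, so the order of treatment does not explain the difference.

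**Working it through.** **Inputs (Tables 1 and 2).** V2 is 7–60 days after V1; V3 is 14–60 days after V2; V4 is 3 days after V3; V5 is 14–60 days after V4; V6 is 3 days after V5. Baseline may fall on day 1. Footnote a allows a baseline test 0–4 whole days before V1 to stand.

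**Reproducing the printed day windows.** Starting from V1 = D1:

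- V2: 1 + 7 to 1 + 60 = D8–61
- V3: 8 + 14 to 61 + 60 = D22–121
- V4: 22 + 3 to 121 + 3 = D25–124
- V5: 25 + 14 to 124 + 60 = D39–184
- V6: 39 + 3 to 184 + 3 = D42–187

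All agree with the tables.

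**Age of the last scheduled test at second-period dosing.**

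| Visit | Calculation | Age (days) |
|---|---|---|
| V2, NF1 | (7 to 60) + (0 to 4) | 7–64 |
| V2, NS, footnote a read as requiring a V1 test when baseline is 5 or more days earlier | (7 to 60) + (0 to 4) | 7–64 |
| V2, NS, Table 1 read literally (no V1 test marked, no limit on the baseline-to-V1 gap) | (7 to 60) + gap | from 7, no printed maximum |
| V5, NS | 3 + (14 to 60) | 17–63 |

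As an illustration of the third row, an assumed 14-day gap would give up to 60 + 14 = 74 days. The Fig. 1 caption allows a 7-day minimum pause in Experiment II, which would lower the V5 minimum to 3 + 7 = 10 days and leave the maximum at 63. On every reading, the youngest possible test at V2 (7 days) or V5 (17 or 10 days) is older than the footnote tolerates before V1.

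**Number of second-period visits without a scheduled test.** At planned size: 14 NS patients × 2 + 14 NF1 patients × 1 = 42. The Trial status section reports that "an actual number of 16 participants have been enrolled" but not the split by group. With at most 14 per group and everyone completing, the count runs from 2 × 2 + 14 = 18 to 2 × 14 + 2 = 30.

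**Expected pregnancies before the active dose, at planned size.** Assumptions, none of them in the document: 1:1 allocation (7 placebo-first patients in each of three experiments, 21 patient-periods); a share *s* of patients who are women of childbearing potential; an annual contraceptive failure rate *f*; every gap at its longest, with 64 days for both groups at V2. Placebo-first woman-periods number 21 × 0.25 = 5.25 to 21 × 0.50 = 10.5.

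Expected number = 14*s*[1 − (1 − *f*)^(64/365.25)] + 7*s*[1 − (1 − *f*)^(63/365.25)]

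- *s* = 0.25, *f* = 0.01: 0.009
- *s* = 0.50, *f* = 0.09: 0.171
- *s* = 1, *f* = 0.09: 0.342

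**The case against.** The best defence is that the tables come from a journal article that condenses a longer protocol. The full German protocol and Additional file 1 are not shown and may require a test or a pregnancy check before every dose. This limits the point to the two printed schedules, but it does not remove it. The article prints a dedicated test row with a retest rule, so it states a schedule, and a reader who follows it would not test at V2 or V5.

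A second defence is that the pattern is deliberate. The article says "Three randomizations take place—one for each experiment", the V3 test coincides with the second NS randomisation, and nothing says that exclusion criteria are re-applied at each dose. In NF1, however, two tests are marked before a single randomisation. Testing at randomisation also protects the first period, whichever treatment it holds, and leaves the second uncovered. Contraception is a continuing safeguard and does lower the risk, but the schedule itself does not treat it as a substitute for testing, since it requires both at entry.

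Third, the tables contain labelling slips (the medication rows in Table 1 swap the experiment numbers, for instance), so a missing mark could be a slip too. That is possible, and is a further reason to ask what was actually done.

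A reader might go further and infer that the plan contradicts itself, that women were in fact dosed untested, or that fetal harm is likely. The documents support none of these. No text promises a test at V2 or V5, conduct at those visits is not reported, and no fetal risk is described for one lamotrigine dose or four days of lovastatin.

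**Conclusion.** The point holds as a minor gap in the printed safety schedule. No pregnancy test is marked before second-period dosing, and a placebo-first woman would take active drug on a test 7–64 days old at V2 (for NS, with that maximum only under the stricter reading of footnote a) or 17–63 days old at V5. The standard against which this falls short is the trial's own: under 5 days before V1, and a fresh test at V3.

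The absolute risk is small, about 0.01 to 0.17 expected pregnancies at planned size and 0.34 even if every patient were a woman of childbearing potential with 9% annual failure. These figures rest on the assumed share, failure rate, longest gaps and 1:1 allocation. With 16 patients enrolled instead of 28, the same assumptions would give less. No efficacy estimate or test is affected.

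**What to change.** Mark a urine pregnancy test for women of childbearing potential before dosing at V2 in Tables 1 and 2 and at V5 in Table 1, and withhold study drug if it is positive. The test age at the first second-period dose then falls to 0 days. If the full protocol already requires this, show it in the tables.

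The cost is three table marks and one dipstick per such woman at each existing second-period visit: 42 × 0.25 to 42 × 0.50, or about 11 to 21 tests at planned size, and 42 at the very most. The test is already in use and no visit is added.

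Because the last visit has taken place, the schedule of this trial can no longer be changed. The results report should state whether tests were done at V2 and V5, and follow-on trials should use the corrected schedule.

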### Transcranial magnetic stimulation (TMS)

Transcranial magnetic stimulation (TMS) is a standard method used in medical diagnostics and research in humans [13, 14]. The planned investigations promise progressing basic findings regarding the neurophysiological mechanisms of the TMS and of neuronal plasticity in patients with NF1 and NS. Planned neurophysiological investigations with TMS delivered by the PowerMAG quadri-pulse stimulation (QPS) device (Mag & More GmbH, Munich) bear only very little risks and have been used by the investigators before [15]. An increased susceptibility to seizures, which can be observed with high-frequency, above-threshold TMS, was not seen so far using the planned stimulation protocols [15]. The clicking noise, which appears using transcranial magnetic stimulation, does not cause any adverse effect. The examination is not painful. Some participants are not used to the involuntary muscle contraction, which appears under magnetic stimulation, and sometimes this is felt as an awkward sensation [14]. However, experience has shown a fast adaption to these contractions. Participants are informed about this beforehand.

No other undesirable side effects are expected during stimulation. The investigators used TMS in patients with NF1 [6] as well as with NS [7] reviewed in [8] to demonstrate deficits in synaptic plasticity which were associated with attention deficits (NF1: [6]). The investigators have a long time experience with TMS and published several manuscripts in international journals [10, 15–17]. The study procedure contains pre-measurements before interventional, repetitive TMS using the quadri-pulse theta burst stimulation protocol (qTBS) [15] and three (Post 1–3) follow-up measurements (Fig. 3). Changes in motor-evoked potentials (MEP), referring to the model of long-term potentiation (LTP)-like plasticity, as primary outcome measure, are monitored until 1 h after interventional TMS, conducted by the qTBS protocol. Changes in local excitability are investigated by the resting motor threshold.

**Fig. 3 Fig3:**

Timeline of TMS measurement. After pre-measurements, patients (NS and NF1) will receive a quadri-pulse theta burst stimulation (qTBS) to evaluate changes in cortico-spinal excitability. Motor evoked potentials (MEP) and resting motor threshold will be monitored 2–5 min, 30 min and 60 min after qTBS. MEP, motor evoked potential; RMT, resting motor threshold; AMT, active motor threshold; qTBS, quadri-pulse theta burst stimulation

### Test for Attentional Performance (TAP)

The computerized Test for Attentional Performance (TAP) battery is a widely used tool in the systematic assessment of attention [6]. Attention skills of the participants are evaluated by conducting the Alertness, Visual Scanning, GoNogo and Incompatibility task. These four subtests of the TAP were selected because of a strong analogy to attention deficit responsive testing in patients with NF1. The Alertness test is a visual reaction time task to a presented visual target stimulus (cross) with or without previous acoustic warning. The Visual Scanning test requires accuracy and performing speed while detecting the target in a field of similar figures. The GoNogo test assesses the ability to discriminate between a target and a similar but irrelevant non-target, where participants have to respond to the target and inhibit their response to the non-target. In the Incompatibility test, participants have to detect the direction of a simple arrow (right/left) by pressing a button on the left or right side regardless on which side of the screen (right/left) the arrow appears.

### Endpoints and endpoint rationale

The *primary endpoint* for each experiment is the difference between the amplitude of the motor evoked potential (MEP) elicited with transcranial magnetic stimulation (TMS, measured at three time points after interventional TMS for each investigation) after placebo and after medication (LTG and LOV).

Changes in MEP are a well-established and safe method to probe changes in cortico-spinal excitability in humans [18]. MEPs are elicited by TMS using a figure-of-eight coil with an outer diameter of 100 mm centred tangentially on the scalp over the primary motor cortex (M1) of the nondominant hand with its handle pointing in a posterior direction and laterally at an angle of approximately 45° away from the midline. MEPs are recorded from the abductor pollicis brevis (APB) muscle at rest by surface electromyography (EMG) using silver/silver chloride electrodes with a surface area of 263 mm^2^ (AMBU, Ballerup, Denmark) mounted in belly-tendon recording technique. Data are band-pass filtered (20–2000 Hz) and amplified using an Ekida DC universal amplifier (EKIDA GmbH, Helmstadt, Germany), digitized at 5 kHz sampling rate using a MICRO1401*mkII* data acquisition unit (Cambridge Electronic Design Ltd, Cambridge, UK) and stored on a standard personal computer for online visual display and later offline analysis using Signal Software version 5 (CED Ltd, UK). MEP size is determined by measuring the two highest peaks of opposite polarity. Twenty trials will be recorded and then averaged for each point of investigation as described elsewhere [15, 16]. Resting motor threshold is recorded to probe changes in local cortical excitability [19].

The *secondary endpoints* for each experiment include the difference between the neuropsychological testing of attention by the TAP and differences in short interval cortical inhibition (SICI) after placebo and after medication (LTG and LOV) [6, 20]. Another endpoint is the comparison of LTG and LOV effects on synaptic plasticity and attentional performance in the NS group. The TAP is a well-established tool and used to measure the influence of LTG and LOV on attention [7, 20]. We previously demonstrated that LOV leads to an amelioration of attentional performance in humans with NF1 [6]. Consequently, we hypothesized that this would also lead to better attention in patients with NS and that LTG ameliorates attention in NF1 and NS.

For SICI, a subthreshold conditioning stimulation is delivered 2, 3 and 5 ms before a test stimulus [6]. It has been demonstrated before that an increased inhibition is the most prominent factor in mice with NF1 to prevent synaptic plasticity [5]. The authors have previously demonstrated that LTG is a potent modulator of synaptic plasticity in healthy humans [10]. Decreasing intracortical inhibition by LOV was associated with an increase in synaptic plasticity in patients with NF1 [6]. The central role of intracortical inhibition regulating synaptic plasticity in NF1 has recently been certified by animal studies revealing a new option of pharmacological intervention with LTG [5]. We have previously shown that LOV leads to a disinhibition in patients with NF1 and, therefore, hypothesized that this would be a key factor to normalize cortico-spinal excitability in patients with NF1 and NS.

*Safety measures* include documentation of blood pressure and heart frequency prior to the intervention as well as monitoring of EMG activity during TMS intervention and documentation of adverse events (AE), severe adverse events (SAE) and suspected unexpected serious adverse reactions (SUSAR) following established definitions and legal requirements. The intensity of AEs is defined according to the common terminology criteria for adverse events (CTCAE Version 4.0, https://www.eortc.be/services/doc/ctc/CTCAE_4.03_2010-06-14_QuickReference_5x7.pdf).

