**Lovastatin LTP (increase in mean MEP) data (Mainberger et al. **[7]**) with common SD of 0.5**			
Healthy controls	1.440	1.600	1.710
NF1	0.920	0.970	0.980
Difference	0.520	0.630	0.730

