**Experiment III**			
Local α	0.050	0.025	0.017
Power with 14 patients	94%	97%	99%
Power with 12 patients	90%	94%	97%

An increase in MEP amplitudes over time is considered to refer to the concept of long-term potentiation (LTP)-like plasticity as it has been demonstrated in Mainberger et al. [7] as well. Twelve patients per disease entity will be enough to provide appropriate power to all planned primary endpoint tests (two-sided paired samples *t*-tests) with a global significance level of 5% and adjusted local significance levels using the Bonferroni-Holm procedure. In order to account for some unobtainable data and drop outs, the sample size will be increased to 14 patients per disease (28 trial participants in total).

Analysis sets: For each experiment, there will be a separate analysis set defined, as it is possible that a patient is suitable for analysis in only one of the first two experiments. All analyses will be performed on the full analysis set (FAS-I, FAS-II, FAS-III), consisting of all patients who delivered a full set of MEP measurements within the corresponding experiment. Since all measurements will take place within a very short time per patient, it is expected that the data will be either complete or entirely missing.

Primary endpoint: The primary endpoint analyses will be performed in three separate testing procedures. The global significance level will be 5%. Since experiments I and II are done on the same set of patients, the significance level for those two experiments will each be 2.5%. The significance level of experiment III will be 5%. The primary endpoint analysis will consist of three series of three paired samples two-sided* t*-tests, comparing MEP under verum vs. placebo at the three measurement time points. The local significance level will be adjusted using the Bonferroni-Holm procedure and will be as follows for the ordered by *p*-value tests:

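### The primary endpoint and its t-tests use only post-qTBS MEP amplitude, while the article elsewhere defines the outcome as a change in MEP, so a drug effect already present before qTBS could be read as plasticity

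*Protocol article*

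**What the plan says.** **The endpoint and the test.** Under Endpoints and endpoint rationale, the primary variable is given as follows: "for each experiment is the difference between the amplitude of the motor evoked potential (MEP) elicited with transcranial magnetic stimulation". The same sentence takes that amplitude at three times following the stimulation, once under placebo and once under drug. Under Analyses and statistics, each experiment gets three two-sided paired t-tests, described as "comparing MEP under verum vs. placebo at the three measurement time points". Neither place has a pre-qTBS term, whether as change, ratio or covariate.

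**The outcome as described elsewhere.**
- The Methods part of the abstract names the primary endpoint as a change in synaptic plasticity.
- The TMS section has "Changes in motor-evoked potentials (MEP), referring to the model of long-term potentiation (LTP)-like plasticity, as primary outcome measure".
- The sample-size table labels its planning data "increase in mean MEP", whereas the sentence introducing that table calls the inputs expected means of MEP amplitudes.
- The text after the table states "An increase in MEP amplitudes over time is considered to refer to the concept of long-term potentiation (LTP)-like plasticity".

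**The measurements.** The TMS section says "The study procedure contains pre-measurements before interventional, repetitive TMS using the quadri-pulse theta burst stimulation protocol (qTBS"), followed by three follow-up measurements. The Fig. 3 caption gives the same order.

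**Drug timing.** LTG or placebo is taken 2 h before TMS in experiments I and III. In experiment II, the dose on the day of TMS is taken 3 h before it.

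**The concern.** The trial asks whether a drug alters the response to qTBS. That response is the difference between MEP after and before the stimulation in one session. A verum-placebo comparison of post-qTBS amplitudes alone adds together two things: the drug's effect on the response to qTBS, and any direct effect on corticospinal excitability that was there beforehand. Since dosing precedes TMS by 2 to 3 h, the pre-qTBS MEP is itself measured under drug, so such a direct effect would carry into all three post-qTBS values.

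Randomised order and within-patient pairing remove stable differences between patients. They do not remove a drug effect on excitability. A shift upwards could look like improved plasticity, and a shift downwards could hide a real improvement. The inconsistency also leaves two analyses, one raw and one baseline-corrected, that could each be presented as the prespecified one.

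**Working it through.** **1. The plan's own power figures.** Inputs from the sample-size table: differences 0.52, 0.63 and 0.73; common SD 0.5; local levels 0.025, 0.025/2 and 0.025/3 (experiments I and II) or 0.05, 0.05/2 and 0.05/3 (experiment III). For a two-sided paired t-test, power comes from the noncentral t with n − 1 degrees of freedom and noncentrality (difference/SD) × √n, with 0.5 taken as the SD of the within-patient difference.

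| Experiment | n | Stated (T1/T2/T3) | Recomputed |
|---|---|---|---|
| I and II | 14 | 89/95/97% | 89.6/94.8/98.0% |
| I and II | 12 | 82/89/94% | 82.6/89.0/94.3% |
| III | 14 | 94/97/99% | 94.9/97.7/99.2% |
| III | 12 | 90/94/97% | 90.6/94.5/97.5% |

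The power arithmetic reproduces, so it is not the problem. It also shows that 0.5 was used as the SD of the paired difference.

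**2. What a pure excitability shift does to the test as written.** Assumptions, none of them given in the documents: no plasticity effect; the drug shifts MEP by b equally before and after qTBS; the SD of the paired post-qTBS difference is 0.5; n = 12. The noncentrality is (b/0.5) × √12 and the two-sided 5% critical value on 11 degrees of freedom is 2.201. Chance that one test is significant:

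| b | Noncentrality | Level 0.05 | Level 0.0167 (strictest, exp. III) | Level 0.0083 (strictest, exp. I and II) |
|---|---|---|---|---|
| 0 | 0 | 5.0% | 1.7% | 0.8% |
| 0.1 | 0.69 | 9.7% | 3.8% | 2.1% |
| 0.2 | 1.39 | 24.5% | 11.9% | 7.3% |
| 0.3 | 2.08 | 47.5% | 28.1% | 19.1% |

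**3. The same situation with a baseline-corrected variable.** With change from the same session's pre-qTBS MEP, b cancels: (post + b) − (pre + b) = post − pre. In simulation (40,000 runs, n = 12, correlation 0.5 between the verum-placebo differences before and after qTBS), rejection at 0.05 was about 5% for b = 0, 0.2, 0.3 and 0.5.

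**4. Why covariate adjustment is not equivalent.** The pre-qTBS value is measured under drug. Adjusting with slope β removes βb and leaves b(1 − β). With equal SDs, β equals the correlation, so half the shift remains at 0.5. Simulated rejection at 0.05 for b = 0.2, 0.3 and 0.5 was about 10%, 15% and 24% at correlation 0.5, and 8%, 10% and 15% at correlation 0.7.

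**5. What the change score may cost.** If 0.5 is already the SD for the increase, the stated power applies unchanged. If it is the SD of the raw post-qTBS difference, the change score has SD 0.5 × √(2(1 − ρ)), where ρ is the correlation between the verum-placebo differences before and after qTBS. At ρ = 0.5 the SD is 0.5 and power is unchanged. At ρ = 0 it is 0.707, and power with n = 12 falls to 51/56/64% (experiments I and II) and 64/69/76% (experiment III).

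**The case against.** **A change was plainly meant.** The TMS section, the abstract and the planning table all point to a change, and the full protocol or analysis plan may set the scale. This stands as a statement of likely intent. It does not remove the contradiction: the article positively fixes the variable, the time points and the test, and these do not match its own description of the outcome. The point is about conflicting text, not about missing detail.

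**No shift is documented.** This also stands. The lovastatin disinhibition that the article cites belongs to SICI, a paired-pulse measure, and does not show that single-pulse MEP moves. If stimulus intensity were reset in each session to reach a common pre-qTBS MEP, the bias would be smaller. The article neither states nor excludes that.

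**Stronger readings a reader might infer.**
- That the endpoint analysed is certainly not the one powered. The article calls the same planning values both amplitudes and increases, so this cannot be decided from the text.
- That the bias can be sized by applying a percentage shift to the NF1 planning values. This treats values labelled as an increase as if they were raw amplitudes. If they are post/pre ratios, a proportional shift of every MEP in a session would leave them unchanged.
- That electrode, coil and day-to-day differences bias the comparison. In a randomised, blinded cross-over they add noise, not bias.
- That using the pre-value must improve precision. The test is already paired, so the within-session correlation across patients is the wrong quantity, and a change score gains only when ρ exceeds 0.5.

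**Conclusion.** The point holds as a contradiction between the primary endpoint and test on one side and the stated outcome and the label of the planning data on the other. Followed literally, the test cannot separate an effect on plasticity from a drug effect on excitability present before qTBS. The possibility of bias follows from the design; its size is unknown. The figures of about 10% to 48% for a single test at 0.05 rest on an assumed shift of 0.1 to 0.3, an SD of the paired difference of 0.5, 12 patients and no plasticity effect. They illustrate sensitivity and do not estimate this trial's error rate. It matters because the choice decides what a significant primary result would mean.

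**What to change.** - Under Endpoints and endpoint rationale, and again in the primary endpoint paragraph of Analyses and statistics, define the primary variable at each of the three times as the change (or the log ratio) from the same session's pre-qTBS MEP, compared verum versus placebo within patient. Choose one of the two scales.
- State the sample-size means and SD on that same scale, and say whether the planning values are amplitudes, differences or ratios.
- Report the drug effect on pre-qTBS MEP and on resting motor threshold separately. State whether stimulus intensity was reset in each session.
- Do not offer covariate adjustment for the pre-qTBS MEP as an equivalent.

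**Cost.** The Trial status section reports that the last visit has taken place, with 16 participants enrolled. The change therefore needs no new visits, only wording, settled before unblinding, and a short additional analysis of collected data. The downside is a possible loss of precision if the verum-placebo differences before and after qTBS correlate below 0.5.
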